**Questionnaires for the partner**					
Socio-Demographic Questionnaire	–	✓	–	–	–
International Index of Erectile Function for Men	–	✓	–	–	–

*T0 = screening, T1 = baseline, T2 = after Session 5 assessed in IG, T3 = posttreatment, T4 = 6-month follow-up*.

#### Sexual Dysfunction Disorders of the Partners

Sexual dysfunction disorders of the partners will be examined using the German version of the International Index of Erectile Function for Men (98, 99). Including 15 items, the questionnaire consists of five subscales: erectile function, orgasmic function, sexual desire, intercourse satisfaction, and overall satisfaction. The first 10 items are rated on a 6-point scale (0–5) with 0 = no intercourse (attempt) and the remaining 5 items are presented with 5-point scales (1–5). High internal consistency has been reported for all subscales with Cronbach alpha between α = 0.71 and α = 0.96 (98, 99).

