### Aims

In this study, we will investigate the efficacy of a newly developed Internet-based guided self-help intervention for GPPPD. We hypothesize that participants in the intervention group (IG) are more likely to achieve intercourse penetration, the primary outcome in this study, from pretest to posttest, compared to a waitlist control group (WCG), and that this effect will also be sustained until a 6-month follow-up. In addition, the study aims (1) to analyze changes concerning secondary outcomes compared to the WCG, (2) to assess predictors and moderators of intercourse penetration and treatment adherence in explorative analyses, (3) to analyze fear of sexuality, penetration-related cognitions, and exercise intensity as mediators of intercourse penetration in the IG, (4) to investigate sexual dysfunctions of partners as a potential moderator of treatment outcome, and (5) to examine patients experiences with the intervention and treatment adherence qualitatively in order to further improve Internet-based interventions for GPPPD.

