### Participants and Procedure

#### Inclusion and Exclusion Criteria

We will include women who (1) have not been able to have sexual intercourse in at least the last 6 months conformed to DSM-5, as indicated by scores ≤ 1 on Primary Endpoint Questionnaire (PEQ) item 7 (60), (2) are at least 18 years of age, (3) whose penetration difficulties are not due to a medical condition, (4) are in a heterosexual relationship or have a heterosexual (training) partner, (5) who have Internet access, (6) have sufficient German skills in reading and writing, and (7) are willing to give informed consent.

We will exclude individuals reporting to have been diagnosed with (1) psychosis or dissociative symptoms in the past or present, (2) posttraumatic stress disorder or traumatization due to sexual abuse in the past or the present, (3) substance abuse or dependency in the present, or (4) moderate or severe depression or bipolar disorder in the present assessed with the Structured Clinical Interview for Diagnostic and Statistical Manual of Mental Disorders (fourth edition) Axis I Disorders (SCID-I) (66), and those (5) currently being treated for GPPPD.

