### Outcome Measures

#### Intercourse Penetration

The seven-item PEQ will be used as a primary outcome measure. Successful intercourse penetration (SIP) will be measured by one item assessing the degree to which the insertion of the partner’s penis was possible. The items will be answered on a 4-point Likert scale (0 = not attempted; 1 = attempted, but unsuccessful; 2 = attempted and sometimes successful; 3 = attempted and always successful). Previous cases of women reaching SIP prior to treatment completion have shown that they are susceptible to study dropout (67). For that reason, participants who do not fill out the PEQ online, (1) are scheduled for a telephone assessment or (2) can report to their eCoach whether intercourse penetration was successful.

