#### Sexual Functioning

To measure different domains of female sexual functioning, the Female Sexual Function Index will be used (75–77). This self-report instrument consists of the following 6 subscales: sexual desire, sexual arousal, lubrication, orgasm, pain and sexual satisfaction. The questionnaire uses a 6-point Likert scale anchored by 0 = no sexual activity and 5. The measure allows for the calculation of specific indexes for each dimension and of an overall sexual function index. The internal consistency ranges from α = 0.82 to α = 0.93 in women with female sexual arousal disorder (76) and from α = 0.76 to α = 0.93 in a sample of women with vaginal penetration difficulties (67).

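### The partner-dysfunction moderator is confounded with whether the couple attempts intercourse, and the planned moderator model cannot separate the two

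*Protocol article*

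**What the plan says.** All references are to the Protocol article.

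- **Aims.** The fourth additional aim is "to investigate sexual dysfunctions of partners as a potential moderator of treatment outcome". The Abstract places the partner measurement at T1 and ties it to the primary outcome.
- **Sexual Dysfunction Disorders of the Partners.** The instrument is the International Index of Erectile Function, with 15 items. On coding: "The first 10 items are rated on a 6-point scale (0–5) with 0 = no intercourse (attempt"; "the remaining 5 items are presented with 5-point scales (1–5". On structure: "the questionnaire consists of five subscales: erectile function, orgasmic function, sexual desire, intercourse satisfaction, and overall satisfaction". No total score is named, and the article does not say which score is the moderator.
- **Inclusion and Exclusion Criteria.** Women qualify if they "have not been able to have sexual intercourse in at least the last 6 months", "as indicated by scores ≤ 1 on Primary Endpoint Questionnaire (PEQ) item 7".
- **Intercourse Penetration.** The two qualifying levels of that item are "0 = not attempted; 1 = attempted, but unsuccessful". The same item measures the primary outcome.
- **Predictor, Moderator, and Mediator Analyses.** Moderators of intercourse penetration are exploratory. Each moderator model holds the baseline variable, the arm and their interaction. A significant interaction is followed by simple slopes at one SD either side of the moderator's mean. Attempt status is not among the terms.

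**The concern.** Ten items of the moderator can be answered informatively only if the couple has had, or attempted, intercourse. The trial selects couples in whom intercourse has not been possible and admits those who have not attempted it. In a couple without attempts, the coding gives the partner the lowest value on those items whether or not he has a dysfunction.

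Whether the couple attempts intercourse is also what separates level 0 from level 1 of PEQ item 7 at baseline. That is the woman's own starting point on the primary outcome item, and it may well be related to how she responds to the program. If the arm effect differs between women who start at 0 and women who start at 1, a partner score driven partly by attempt status will show an interaction even when partner function plays no role. The result would be reported as an effect of partner dysfunction. The article's Strengths section presents the partner questionnaire as a major advantage, so the aim deserves an analysis that can support its label.

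**Working it through.** The article states no figure on this point, so there is none to reproduce. The check is arithmetic on the item ranges, followed by a labelled illustration.

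**Inputs from the article:** ten items scored 0 to 5, with 0 for no intercourse or attempt; five items scored 1 to 5; eligibility at PEQ item 7 = 0 or 1.

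**Step 1, the ten items alone.** A partner who answers 0 throughout has a sum of 10 × 0 = 0. A partner whose couple attempts and who gives the lowest non-zero answer throughout has 10 × 1 = 10. Every all-zero partner therefore ranks below the poorest-functioning attempting partner. The same holds within any subscale built only from these items.

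**Step 2, all 15 items summed (assumption: the article names only subscales).**
- Minimum: 10 × 0 + 5 × 1 = 5. Maximum: 10 × 5 + 5 × 5 = 75. Range: 75 − 5 = 70.
- Partner with zeros on the ten items: between 5 and 5 × 5 = 25.
- Partner with the best answer on every item: 75 if the couple attempts, 25 if it does not. The loss is 50 points, and 50/70 = 71% of the range, with no dysfunction present.

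**Step 3, how much of the spread could be attempt status.** The share *a* of couples without attempts is not given, nor is the distribution of scores. Assume, for illustration only, that the ten-item sum has mean 40 and SD 8 in attempting couples and is 0 in the others. Then

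- variance between the two groups = a(1 − a) × 40²
- variance within attempting couples = (1 − a) × 8²
- share due to attempt status = between / (between + within)

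| a | between | within | share |
|---|---|---|---|
| 0.10 | 144 | 57.6 | 71% |
| 0.25 | 300 | 48 | 86% |
| 0.50 | 400 | 32 | 93% |
| 0.75 | 300 | 16 | 95% |

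At a = 0.25 the overall mean is 0.75 × 40 = 30 and the SD is √348 ≈ 18.7. The planned simple slopes would then be read at about 11 and 49. The lower point falls between the non-attempters at 0 and the bulk of the attempters around 40, so the two slopes would mainly contrast couples without attempts with couples with attempts. At a = 0 the problem disappears.

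**Step 4, the model.** With only the moderator, the arm and their interaction, any difference in arm effect by attempt status is absorbed by the moderator interaction to the extent that the two are correlated. No planned term takes it out.

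**The case against.** **Attempting couples are eligible too.** A woman at PEQ item 7 = 1 has attempted without success, and her partner can give non-zero answers. Five of the 15 items have no zero at all. This stands. A reader might infer that the questionnaire measures lack of attempts instead of partner dysfunction. The documents support only confounding, of a size they do not reveal.

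**The article does not show that PEQ item 7 = 0 forces ten zeros.** It paraphrases the zero label in one line for all ten items and gives no recall period for the partner questionnaire, so the two instruments may cover different windows. This also stands. It makes the overlap imperfect, but it does not remove it, and it is a reason to use the partner's own zeros as well as the PEQ item in the remedy.

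**Scoring detail may sit in a fuller plan.** The choice of subscale and the handling of inapplicable answers can fairly be left there, and their absence is not the point. The point rests on what the article fixes: an intercourse-dependent instrument, its zero code, a population admitted at the no-attempt level, and moderator terms that leave attempt status out.

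**The Female Sexual Function Index seems to share the fault.** A reader might infer this from "The questionnaire uses a 6-point Likert scale anchored by 0 = no sexual activity and 5". The documents do not support it. That zero refers to sexual activity in general, which the eligibility rule does not exclude. The index is a secondary outcome in the women, not the partner moderator, and a move from no activity to some activity may be real improvement.

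**The analysis is exploratory.** True, and this limits the weight of the point.

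**Conclusion.** The point holds as a confounding problem in one exploratory moderator analysis. Under the stated coding and model, not attempting intercourse counts as the poorest partner function, and an interaction with the partner score cannot be attributed to partner dysfunction.

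The size is open. The ceiling of 25 out of 75 assumes a 15-item total and zeros on all ten items. The variance shares of 71% to 95% rest on an assumed mean and SD and on assumed shares of non-attempting couples from 10% to 75%. The actual effect depends on how many women enter at PEQ item 7 = 0. It would not be correct to say that aim 4 will be answered wrongly, only that the planned model could not show whether it had been. The chi-square comparison of the primary outcome between arms does not use the partner score and is unaffected.

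**What to change.** 1. Add baseline PEQ item 7 (0 versus 1) and its interaction with arm to the partner-moderator model. Table 2 has the PEQ at T1, the same visit as the partner questionnaire.
2. Repeat the analysis with the no-intercourse-or-attempt answers treated as not applicable: intercourse-dependent subscales only in couples with attempts, and the items without a zero option in all couples.
3. Report the number of women at PEQ item 7 = 0 and 1 by arm, and the number of partners with zeros on the ten items, so that the reader can judge the overlap.
4. Interpret an interaction as one of partner dysfunction only if it persists in steps 1 and 2.

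All of this uses data already collected. The cost is precision: step 1 adds terms correlated with the moderator, and step 2 leaves fewer partners or fewer items. The items without a zero may also cover less of what aim 4 means by dysfunction. A null result after these steps would therefore be weak evidence of no moderation and should be reported as such.

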#### Adherence Measures

Adherence will be assessed by session completion (0–8) tracked by the system of the intervention platform. Participants will also be asked to report how often they completed the exercises in a given week with one item measured on a 4-point Likert scale ranging from 0 = less than once a week to 3 = every day.

### Qualitative Interviews

The aim of the qualitative interview will be the qualitative assessment of factors regarding the intervention efficacy and adherence in order to further improve Internet-based interventions for GPPPD. Telephone interviews will be conducted with all willing intervention completers as well as participants who ceased to complete the intervention. The interview assesses different aspects with regard to Internet-based GPPPD treatment including (1) participants’ expectations and hope of improvement, (2) perceived usefulness of the treatment, (3) reasons for treatment success and failure, (4) reasons for treatment adherence and non-adherence, (5) usability and layout, (6) quality and content of the intervention and the guidance, and (7) overall strengths and limitations of the program. The evaluation relies on qualitative content analyses by Mayring (100) and Kuckartz et al. (101).

### Sample Size Calculation

We aim to include 200 participants to statistically detect a minimal clinical relevant effect size of *w* = 0.20, with a power (1 − β) of 80% and an alpha of 0.05 (two-tailed test) for an intention-to-treat analysis using G*Power. The design of the study is based on the expected superiority of the IG compared to the WCG on the primary outcome variable (i.e., sexual intercourse) at posttreatment (T3).

### Statistical Analyses

#### Clinical Effectiveness

Analyses will be conducted and reported in accordance with the statement by Consolidated Standards of Reporting Trials (102). Data will be analyzed on an intention-to-treat basis. Additionally, study completer analyses including only participants who filled out the questionnaires and intervention completer analyses including only participants who have completed the 8 treatment sessions will be conducted. Missing data will be handled using multiple imputations (MIs) calculated by a Markov Chain Monte Carlo multivariate imputation algorithm of 100 estimations per missing value. MI is especially robust with respect to missing data (103). We will use chi-square test (χ^2^) to examine differences in the primary outcome. Differences in secondary outcome measures will be analyzed between and within the two study groups based on regression. For all analyses, Cohen’s *d* (104), including 95% confidence intervals, will be calculated for the differences between baseline and follow-up scores calculated by using the mean difference in change between the IG and WCG divided by the pooled standard deviation of the change score. For all statistical analyses, the significance level will be set at p < 0.05, 2-sided. All analyses will be performed with IBM SPSS v. 24.

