**Main outcome measures:**

The primary outcome will be sexual intercourse involving the insertion of the partner’s penis at posttreatment. Secondary outcomes include, e.g., improved non-intercourse penetration, sexual functioning, dyadic stress coping, reduced fear of sexuality and negative penetration-related cognitions. Fear of sexuality, penetration-related cognitions, and exercise intensity will be assessed as mediators of intercourse in the IG. Sexual dysfunctions of partners will be measured at baseline (T1) and investigated as a potential moderator of the primary treatment outcome.

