#### Stepwise Procedure: Assessment of Eligibility and Randomization

Women who sign up as potential participants will receive an online information letter with detailed information on the study procedures. They will be asked to provide an email address that they want to use for the study and a first and last name (which can be pseudonyms if desired). The women will be informed that they can withdraw from the intervention and/or study at any time without any negative consequences. Applicants who intend to participate in the study will be asked to complete online screening questionnaires that assess inclusion and exclusion criteria. If responses to this questionnaire indicate that participants might be affected by one of the mental health disorders listed as exclusion criteria above, participants will be scheduled for the SCID-I *via* telephone. Women who meet all of the inclusion criteria and none of the exclusion criteria and who complete the baseline assessment and return the informed consent form will be considered for the study and randomly allocated to one of the two study conditions. Randomization will take place at an individual level. This process will be completed by an independent researcher not otherwise involved in the study using an automated computer-based random integer generator (randlist). Until this process has been completed, the results will not be known by participants, researchers involved in recruitment or eCoaches. Participants will be informed of the outcome of the randomization, and participants in the IG will receive immediate access to the program. Participants in the WCG will receive access to the program 6 months after study intake.

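### The primary success outcome gets a chi-square test and a change-score Cohen's d, but no risk difference or odds ratio that can be pooled over the imputations

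*Protocol article*

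**What the plan says.** The abstract of the protocol article defines the endpoint: "The primary outcome will be sexual intercourse involving the insertion of the partner’s penis at posttreatment". Under Intercourse Penetration, success is read from one PEQ item with four levels: "0 = not attempted; 1 = attempted, but unsuccessful; 2 = attempted and sometimes successful; 3 = attempted and always successful". Under Inclusion and Exclusion Criteria, women enter only with a score of 0 or 1 on PEQ item 7, so nobody is a success at baseline.

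Under Clinical Effectiveness, the primary test is given in one sentence: "We will use chi-square test (χ^2^) to examine differences in the primary outcome". No covariate is named, whereas secondary outcomes are to be analysed by regression. Missing data are multiply imputed 100 times. One effect measure is prescribed for all analyses, Cohen's d with a 95% confidence interval, and its denominator is the pooled SD of change. It "will be calculated for the differences between baseline and follow-up scores calculated by using the mean difference in change between the IG and WCG". No risk difference, risk ratio or odds ratio is named.

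The Sample Size Calculation section says "We aim to include 200 participants" for a "minimal clinical relevant effect size of *w* = 0.20", with 80% power and two-sided alpha 0.05.

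**The concern.** The primary question is how many more women achieve intercourse with the program than on the waiting list. The planned outputs are a chi-square p-value and a standardized difference in mean change, and neither answers that question directly. A risk difference or odds ratio with a confidence interval would.

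The choices also fit poorly with each other. Rubin's rules combine an estimate and its standard error across imputed datasets. A chi-square statistic alone supplies neither, so the primary result would need a special combination method, while a regression coefficient or risk difference would pool in the standard way. At stake is how clearly the headline result can be read and how it is carried through the imputation, not whether a two-by-two test is legitimate.

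**Working it through.** **1. Reproduce the sample size.** Inputs from Sample Size Calculation: w = 0.20, power 80%, two-sided alpha 0.05. Formula: N = λ/w², where λ is the noncentrality that gives 80% power for a chi-square test.

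- One degree of freedom (success by arm): λ = 7.849, N = 7.849/0.04 = 196.2, so 197. Power at 200 is 80.7%.
- Three degrees of freedom (all four levels by arm): λ = 10.903, N = 10.903/0.04 = 272.6, so 273. Power at 200 is 65.4%.

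Only the two-by-two comparison comes near 200.

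**2. What d conveys on the success indicator.** Everyone starts as a non-success, so change equals success at T3, and d is the risk difference over the pooled standard deviation. With equal arms (1:1 is assumed, as the ratio is not stated), d = 2w/√(1 − w²) = 0.40/√0.96 = 0.408 at any control rate. The article gives no event rates, so a range is assumed:

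| Control success | Intervention success at w = 0.20 | Risk difference (points) | Odds ratio | d |
|---|---|---|---|---|
| 2% | 12.3% | 10.3 | 6.9 | 0.41 |
| 5% | 17.7% | 12.7 | 4.1 | 0.41 |
| 10% | 25.2% | 15.2 | 3.0 | 0.41 |
| 20% | 38.2% | 18.2 | 2.5 | 0.41 |
| 40% | 60.0% | 20.0 | 2.25 | 0.41 |

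One value of d covers all five rows. By contrast, 25% against 10% with 100 per arm would read as a risk difference of 15 points, with half-width 1.96 × √(0.25 × 0.75/100 + 0.10 × 0.90/100) = 0.103, so a 95% interval of about 5 to 25 points.

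**3. What d conveys on the raw 0–3 item.** Illustrative distributions over scores 0/1/2/3, with baseline assumed half 0 and half 1 (variance 0.25) and independent of the T3 score:

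- Intervention 20/60/15/5%, control 50/30/15/5%. Success is 20% in both arms. Means are 1.05 and 0.75, variances 0.5475 and 0.7875. d = 0.30/√(0.6675 + 0.25) = 0.31.
- Intervention 50/20/25/5%, control 30/55/10/5%. Success is 30% against 15%. Means are 0.85 and 0.90, variances 0.9275 and 0.59. d = −0.05/√(0.75875 + 0.25) = −0.05.

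So d on the raw item can be positive with no difference in success, and slightly negative when success doubles.

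**4. The chi-square over imputations.** Suppose, as an illustration the article does not state, that the chi-squares were simply averaged and compared with 3.84. With a fraction m missing, no auxiliary information and f = m/(1 − m), the null rejection rate is P(χ²₁ > (3.84 − f)/(1 + f)):

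| Missing (assumed) | 10% | 20% | 30% | 40% |
|---|---|---|---|---|
| Type I error | 6.7% | 9.0% | 12.2% | 16.8% |

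Valid combination rules avoid this inflation, as does pooling a log odds ratio or risk difference.

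**5. What baseline adjustment could add.** Simulated power at N = 200 (1,500 trials per setting), unadjusted chi-square against adjusted logistic regression, at success rates close to w = 0.20:

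| Assumed covariate log odds ratio per SD | 10% vs 25.4% | 20% vs 38.5% |
|---|---|---|
| 0 | 83.5 → 83.6% | 82.9 → 83.2% |
| 0.5 | 82.3 → 83.2% | 82.5 → 84.1% |
| 1.0 | 82.6 → 87.3% | 83.3 → 89.7% |

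The gain is about 0 to 6 points.

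**The case against.** The strongest defence is that test and sample size agree. A chi-square on success by arm is valid under individual randomization, and it is the test that 200 women were planned for. This stands. A reader might infer that the chi-square does not fit the endpoint, but the documents do not support that.

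A reader might also fear that all four levels will be tested, so that a move from not attempting to attempting without success could count as a positive trial. The text points away from this. The endpoint is named as successful penetration, the level labels split at 2, eligibility treats scores of 0 and 1 as inability, and only one degree of freedom reproduces the sample size. The cut is not written out, but a four-level test is not what the plan describes.

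Three further limits stand:
- On the success indicator d is not meaningless. It is the risk difference on another scale.
- Dichotomized baseline success is constant, so the lack of adjustment is a missed efficiency, not an error.
- Methods for combining chi-squares exist, a condensed article may leave the rule to the analysis plan, and telephone or eCoach reports of the primary item should limit how much is imputed. Chi-square and imputation are therefore not incompatible.

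Nor can a loss of precision for secondary outcomes be inferred from the change-score d. Those outcomes are to be analysed by regression, and d only standardizes the result.

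The promise of CONSORT reporting helps, but it does not displace an explicit instruction to use d for all analyses.

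**Conclusion.** The point holds in a limited form. The plan prescribes an effect measure that does not express the primary result as a difference in success, and it pairs multiple imputation with a test that gives nothing to pool by the standard rules. The primary test itself is valid and has 80.7% power at 200.

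The same d of 0.41 stands for risk differences from about 10 to 20 points as the control rate goes from 2% to 40%. If d were taken on the raw item, it could diverge from success altogether. These figures rest on assumed event rates and score distributions, 1:1 allocation and, for the power gain of 0 to 6 points, assumed prognostic strength; the article gives none of these. This is a reporting and efficiency improvement that should be made, and it does not invalidate the trial.

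**What to change.** - Define successful intercourse penetration as PEQ item 7 of 2 or more at T3. This mirrors the eligibility rule of 1 or less and the one-degree-of-freedom sample size.
- Estimate the effect by logistic regression on arm, adjusted for baseline PEQ item 7 (0 vs 1) and the baseline non-intercourse PEQ score, and pool by Rubin's rules.
- Report the marginal risk difference and the odds ratio, each with a 95% confidence interval.
- Keep the two-by-two chi-square as a check.
- Restrict Cohen's d to the continuous secondary outcomes.

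The cost is a few sentences of analysis text and slight extra programming. The PEQ is already collected at baseline and T3, so no new data are needed and the sample size is unchanged.
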